### Randomization and allocation

Eligible patients will be randomly divided into the ART 100-mg group, ART 50-mg group, or placebo group at a ratio of 1:1:1. Random numbers will be generated and sorted by independent statisticians using SAS 9.4 (SAS Institute Inc.), and then the patients will be divided into three groups based on the remainder of the number divided by 3. The randomized numbers, rank order, and grouping will be stored in opaque envelopes with serial numbers, which will be kept by the independent researchers and statisticians throughout the study. Envelopes and study drugs will be provided to enroll patients separately by independent blinded researchers.

### Blinding

In this study, a double-blind approach will be applied to the patients and physicians. ART and placebo will be placed in packaged capsules with an identical appearance and distributed to the patients by independent researchers. At the end of the study, independent professional statisticians will be unblinded for the first time and will perform a preliminary analysis of the three sets of outcome data. A second unblinding will be applied to confirm the group and the effect. If serious adverse events occur during the study period, patients will be treated with emergency unblinding and relevant treatment according to the situation.

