#### Withdrawal criteria

The subjects who no longer meet the inclusion criteria, have poor compliance, need immunosuppressive therapy, or have any other reason for violation of the protocol will be monitored by the investigators. These patients will be required to continue regular study visits as scheduled in the protocol after discontinuation of treatment. The data that need to be recorded is the end-point events and safety data that occurred during the duration of this trial.

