#### Termination criteria

Patients will be removed from the study if they develop severe liver or kidney damage during the trial (ALT or AST exceeding twice the normal upper limit, acute kidney injury), severe clinical discomfort caused by the drug (such as severe nausea and vomiting, severe dizziness, and headache), and severe drug allergies. All criteria and decisions will be jointly determined by two or more physicians with the title of deputy chief or higher.

Potential trial participants will be recruited from the six hospitals listed in Supplement Table 2. To reach the target sample size, the trial will be advertised in living communities by local healthcare professionals. We will also utilize advertising via brochures, flyers, or other means suggested through the clinic sites as appropriate. Before each interview, we described the aims of the study, guaranteed confidentiality, and obtained written informed consent. The interviews and examinations were achieved on the premises of the treatment hospital.

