### Safety assessment

The safety assessment includes any serious adverse event and any general adverse event according to the WHO acute and subacute side effects of the performance and indexing criteria for assessment [24]. All records, including adverse events and laboratory test results from the subjects, will be evaluated and followed up until resolved by a medically qualified investigator. The patient’s vital signs and any clinical discomfort will be monitored throughout the study period. Patients who are harmed during this study will receive the necessary medical treatments, such as changing the treatment plan, dealing with complications on time, etc., and the appropriate insurance will cover the expenses.

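### The only stated trigger for emergency unblinding is a serious adverse event, with no condition that managing the event depends on the allocation and no statement of who is told

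*Protocol article*

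**What the plan says.** The Blinding section of the protocol article sets the aim: "In this study, a double-blind approach will be applied to the patients and physicians". It places the planned opening of the codes at the close of the trial: "At the end of the study, independent professional statisticians will be unblinded for the first time". It then adds one rule for breaking the code earlier: "If serious adverse events occur during the study period, patients will be treated with emergency unblinding and relevant treatment according to the situation".

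The Safety assessment section does not narrow the class of event that could set this rule off: "The safety assessment includes any serious adverse event and any general adverse event". It also leaves work to be done after an event has occurred, since records "will be evaluated and followed up until resolved by a medically qualified investigator".

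The Termination criteria include removal for "severe clinical discomfort caused by the drug", decided by at least two senior physicians. Under the Withdrawal criteria, patients who come off treatment are still seen: "These patients will be required to continue regular study visits as scheduled in the protocol after discontinuation of treatment". The Statistical analysis section analyses all results by intention to treat.

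**The concern.** An emergency code break exists for the case in which a patient cannot be managed properly without knowing what was given. The rule as written ties it instead to the seriousness of the event. Many serious events, such as an admission for a fracture, would be managed in the same way whichever arm the patient is in. Opening the code for those gains nothing for the patient and gives up the blind.

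At stake are the decisions still to be made about that patient. Some need judgement, and one explicitly needs a view on whether the drug was the cause. If those who decide know the allocation, the same symptoms can lead to different decisions in different arms. The unblinding would also follow an event that occurs after randomisation and may not be equally frequent in the three arms.

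**Working it through.** No arithmetic applies. The point concerns the wording of a rule, and no sample size, power or error rate depends on it. The check is to read the rule and then see what elsewhere in the article limits it or depends on it.

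1. **The trigger.** The conditional clause of the sentence in Blinding names one thing only: that a serious adverse event occurs. No second condition on the need for the allocation follows.

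2. **The qualifier.** The phrase about the situation comes directly after the mention of treatment. It may govern the treatment alone, or both the unblinding and the treatment. On the first reading, unblinding follows from the event. On the second, unblinding is case by case, but with no criterion. Neither reading states when a code should stay closed.

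3. **The scope.** Safety assessment covers all serious events, not only related or unexpected ones. Neither that section nor Blinding confines the unblinding rule to a subset. No other section at hand does so either; one part of the article, next to Safety assessment, was not available for this check.

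4. **Who is told.** Blinding does not say. Randomization and allocation keeps the grouping in numbered opaque envelopes held by independent researchers and statisticians. A custodian outside the treating team therefore exists, but the rule does not say to whom that custodian discloses.

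5. **What remains open after the event.**
   - *Termination criteria:* the item on "severe clinical discomfort caused by the drug" needs a causal judgement. In a patient known to be on placebo it cannot logically be met; in a patient known to be on artesunate it can. The physicians who decide are not stated to be blind or separate from the care team.
   - *Withdrawal criteria:* poor compliance and the need for immunosuppression are partly matters of judgement.
   - *Interventions:* antihypertensives, diuretics and statins are permitted, so background treatment can change during the trial.
   - *Safety assessment:* the investigator goes on evaluating events until they resolve.

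6. **Whether later data count.** Patients who stop treatment under the Withdrawal criteria keep attending visits, and the analysis is by intention to treat. Serious events that meet none of the Termination criteria do not by themselves remove a patient. Data gathered after a code break can therefore enter the comparison between arms.

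7. **How many patients.** The article plans 120 participants, 40 per arm, and gives no expected rate of serious events. The number of codes that would be opened cannot be calculated from it. Steps 1 to 6 do not need that number.

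**The case against.** The strongest reply is that the sentence is ambiguous and the article condensed. The closing phrase can cover the unblinding as well as the treatment, and the word for emergency itself suggests urgent need. On that reading the rule is already case by case, and what is missing is operational detail that a full protocol would carry.

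Part of this stands. A reader might infer that every serious adverse event automatically unblinds both the patient and the treating physician. The documents do not support that: the qualifier may reach the unblinding, and the text names no one who is told. Nor does the sentence contradict the statement that statisticians are first unblinded at the end, because that concerns a different group of people.

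A reader might also infer that the safety comparison and the proteinuria comparison are biased as planned. That too goes beyond the text:
- Adverse events are to be compared as counts and percentages, and no analysis by causality is stated, so skewed causality ratings do not enter the stated test. The event that triggers the code break has by then already occurred.
- The primary outcome is a 24-hour laboratory measurement, and data collection and preliminary evaluation are assigned to an independent third party.
- Several Termination criteria are laboratory or clinical findings that need no view on cause. Patients who meet them leave the study, so few later decisions remain for them.
- Continued visits and intention-to-treat analysis are already largely provided for.

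The claim of mere missing detail does not stand. The article states a rule and gives its trigger. Staff who follow that rule literally would open codes without need, and the six recruiting hospitals could apply the qualifier differently.

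**Conclusion.** The point holds as a defect in a stated rule. On its plain wording, the seriousness of an event is enough to open the code, and nothing ties the opening to a need to know the allocation or limits who is told. What is exposed is the later judgement on stopping, withdrawal, co-treatment, adherence and adverse events in patients who remain under observation. Direct measurement bias in proteinuria is limited.

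The size cannot be stated. Any count of unblinded patients would rest on an assumed serious-event rate, and the documents give no basis for one. Nor do they allow an estimate of how many code breaks a narrower rule would avoid. If serious events are few, the effect on the primary comparison could be very small.

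The conclusion rests on two assumptions: that site staff apply the sentence as written, and that no narrower rule stands in a full protocol or in the part of the article that was not available. It is an inexpensive improvement worth making, not a threat to the validity of the trial.

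**What to change.** Reword the sentence in Blinding so that:
- serious adverse events are managed and assessed under the blind by default;
- an individual code is opened only when the treating physician states that knowing the allocation is needed to manage that event;
- the allocation is disclosed only to those who need it, through the independent envelope holders already named in Randomization and allocation;
- the causality assessment is recorded before the code is opened where urgency permits, and otherwise the reason it was not is noted;
- each opening is logged with its reason.

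No change to follow-up or to the analysis set is needed. The cost is a short amendment and one documentation step at each code break. Access to emergency unblinding is kept in full, and no rule on the treatment of events is altered.

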### Interventions

The intervention will consist of ART 100-mg group oral 50 mg ART tablets twice a day, ART 50-mg group oral 25 mg ART tablets twice a day, and placebo group oral equivalent placebo twice a day. The ART tablets and placebo will be provided by Guilin Nanyao Co., Ltd. All patients will receive standard support treatment for IgA nephropathy, including adequate RAAS blockers and blood pressure control. Permissible combination antihypertensive medications include diuretics, calcium channel blockers, and β-receptor blockers. Hydrochlorothiazide or loop diuretics could be used when antihypertensive targets are difficult to achieve. Statins and aspirins are also allowed when necessary. Prohibited drugs include proprietary Chinese drugs that may reduce proteinuria (such as *Tripterygium wilfordii*, *Penicillium notatum*, Huangkui capsules, nephritis rehabilitation tablets, Haikun Shenxi capsules), corticosteroids, and any immunosuppressants (such as mycophenolate mofetil, cyclophosphamide, azathioprine, HCQ).

### Outcome measurements

The primary outcome is defined as the percentage change of proteinuria in all three groups after 6 months of intervention. Secondary outcomes include the changes in urinary protein creatinine ratio (UPCR), eGFR, and serum Gd-IgA1 levels in all three groups from baseline. The clinical characteristics of the patients will be collected at baseline before enrollment, including age, sex, age, course of the disease, combined disease, medication history, and so on. Throughout the follow-up, patients will be asked to provide urine and blood samples, which will be collected independently at visit 4 and visit 8, which will be collected for the following: collection, storage, and distribution of biological samples and related data for scientific research in the biobank of Dongzhimen hospital. In order to assess drug compliance, participants will be checked for the remaining number of drugs at each follow-up visit. Patient compliance will be calculated as the percentage of the actually taken number of tablets (distributed pills − returned pills) to the distributed number of drugs.

### Safety assessment

The safety assessment includes any serious adverse event and any general adverse event according to the WHO acute and subacute side effects of the performance and indexing criteria for assessment [24]. All records, including adverse events and laboratory test results from the subjects, will be evaluated and followed up until resolved by a medically qualified investigator. The patient’s vital signs and any clinical discomfort will be monitored throughout the study period. Patients who are harmed during this study will receive the necessary medical treatments, such as changing the treatment plan, dealing with complications on time, etc., and the appropriate insurance will cover the expenses.

### Data collection and management

Each participant will receive a unique identifier upon study entry. This identifier will be used for all data documentation to ensure the participant’s confidentiality. The entire data collection and preliminary evaluation of the results will be performed by an independent third party. The data will be collected in the form of a case report form (CRF) and then reviewed and stored by the lead researcher in each center. Two researchers will independently convert the original data into electronic storage data to ensure the accuracy of the data. A Data Safety Monitoring Board (DSMB) comprised of independent members, including a statistician and a clinician, has been set up to improve the integrity and credibility of the results. All relevant documentation will be retained so that the safety and key efficacy outcomes can be retrospectively evaluated in the future. No specific interim analysis is foreseen for efficacy unless required by the Steering Committee or DSMB because of safety concerns.

#### Protocol amendments and publications

Important protocol modifications will be communicated to each of the authors and other relevant study investigators and will be updated on ClinicalTrials.gov. IRB approval will be obtained before any important protocol modifications will be implemented. Participants will be notified should any important protocol modifications would concern them. The results from the trial will be submitted for publication in a peer-reviewed journal irrespective of the outcome. The final report will follow the CONSORT 2010 guidelines. Authorship of presentations and reports related to the study will be in the name of the collaborative group.

### Sample size

This is a double-blind, randomized, three-group-parallel, placebo-controlled clinical study, and the sample size estimates were based on the change in proteinuria levels. According to the study results when using similar types of drugs (HCQ) for the treatment of IgA nephropathy [12, 25], the average baseline proteinuria was 2.0±0.8 g/day, and 36 participants in each arm could provide 90% of the detection ability, assuming that the placebo group level of proteinuria had not changed, and the ART treatment detected a 25% reduction in proteinuria (ART group: 0.5±0.5 g/day). Assuming that the two doses of the ART group has the same efficacy (the ratio of the ART group to the placebo group is 2:1), and a 10% dropout rate with a type I error rate of 0.05, we plan to enroll 120 participants (40 in each group) in the study.

### Statistical analysis

All results will be analyzed based on an intention-to-treat (ITT) analysis. Normally distributed data will be expressed as the mean ± standard deviation (SD), while nonnormally distributed data will be expressed as the median of the interquartile interval (IQR). Categorical data will be summarized as counts and percentages. The Shapiro-Wilk test will be performed to determine the normal distribution of continuous variables. For the comparison of baseline characteristics between groups, continuous variables (standard normal distribution) will be analyzed by a one-way ANOVA, continuous variables (nonstandard normal distribution) and ordered categorical variables will be tested by the Kruskal-Wallis *H* test, and unordered categorical variables or count variables will be tested by the chi-square test and Fisher’s exact test.

For the effectiveness outcomes, the primary outcome of proteinuria will be described by the percentage change of 24-h proteinuria test results at each visit from baseline, and the secondary outcomes of UPCR and eGFR will be described by the mean difference between the test results of each visit and the baseline. A paired-samples *t*-test or the Wilcoxon signed-rank test will be used for comparisons within groups at each visit time point from baseline, and one-factor ANOVA and the Kruskal-Wallis *H* test will be used for comparisons among groups at each visit time point.

For the safety indicators, adverse events will be described according to the number of cases and percentage, and the chi-square test and Fisher’s exact test will be used to analyze the differences between groups. The missing values will be filled up by the last-observation-carried-forward method. For the initial analysis, we will not adjust for confounders or stratification, and for the secondary analysis, we will adjust for confounders for subgroup analyses, such as baseline proteinuria (3 g/day), renal function (eGFR 45 m1/min per 1.73 m^2^), blood pressure level (systolic blood pressure 140 mmHg), MEST-C classification [26], and the new international risk-prediction score [27]. SAS 9.4 (SAS Institute Inc.) will be used as the statistical analysis tool. A 2-sided *P* < 0.05 will be defined as statistically significant.

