Artesunate (ART) is a derivative of artemisinin (ARS), a component extracted from the traditional Chinese herb *Artemisia annua L.*, with improved pharmacological properties. ART has similar immunomodulatory effects to other antimalarial drugs [17], such as hydroxychloroquine (HCQ) and chloroquine (CQ), but has different active ingredients, which leads to the lack of risk of visual loss caused by HCQ [18]. Many experimental pieces of evidence have shown that ARS and its derivatives (ARSs) have good anti-inflammatory and immunomodulatory functions in SLE, rheumatoid arthritis, multiple sclerosis, inflammatory bowel disease, and other immune diseases [19]. ARS has been shown to improve podocyte injury, improve podoid fusion, and upregulate the expression of Nephrin and Podocin proteins in the podocytes of adriamycin nephropathy mice [20], and SM934 (an ARR) can reduce proteinuria, circulating antibodies, immune complex deposition in tissues, and podocyte injury and finally delay the progression of membranous nephropathy by inhibiting TGF-β1 expression and reducing the Smad2/3 expression pathway in Heymann nephritis mice [21]. More importantly, there is experimental evidence that ART combined with HCQ can effectively reduce 24-h urinary protein, IgA, and IgG immune complex deposition in the glomeruli of IgAN rats to reduce kidney damage through the NF-κB/NLRP3 signaling pathway [22]. Therefore, we hypothesized that ART might have the same excellent effects as HCQ in alleviating kidney injury and reducing proteinuria by inhibiting the activation and proliferation of B cells, inhibiting the generation of Gd-IgA1, and inhibiting inflammatory cytokines.

However, although a large amount of experimental evidence has been accumulated, there is still a lack of randomized controlled clinical trials to verify the potential effect of ART in the treatment of IgA nephropathy. This multicenter, double-blind, randomized, placebo-controlled study was designed to estimate the efficacy and safety of ART in IgA nephropathy. We present this protocol, which was prepared in accordance with the SPIRIT reporting checklist.

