## Discussion

Increasing attention has been given to the application of antimalarial drugs in kidney damage. Given that HCQ has been reported to have a good anti-proteinuria effect in IgA nephropathy patients and that ART has better pharmacological properties than HCQ [28], it is reasonable to believe that ART has the potential to treat IgA nephropathy. Therefore, we designed this double-blind, randomized, three-group-parallel, placebo-controlled clinical trial to evaluate the efficacy and safety of oral ART versus placebo in patients with IgA nephropathy characterized by a high risk of progression in the context of conventional adequate RAAS blocker therapy.

To date, there have been few clinical trials in China on ARSs for the treatment of renal diseases, and only two observational clinical studies on lupus nephritis have reported that ARSs can significantly reduce proteinuria and regulate immune function in patients with lupus nephritis [29, 30]. Studies on the treatment of IgA nephropathy with ART have been mainly based on animal models and cell experiments, and a large amount of laboratory evidence has shown that the effect of ART on IgA nephropathy may be primarily due to its strong anti-inflammatory and immune-regulatory properties, as well as its ability to regulate oxidative stress [31]. Animal experiments found that the combination of ARS and HCQ can reduce the levels of 24-h urine protein, IgA, and IgG immune complex deposition in the glomerulus through NF-κB/NLRP3 signaling [22] and improve the barrier function of the glomerular filtration membrane by regulating the immune response in IgA nephropathy rats [32]. One team demonstrated that dihydroartemisinin (the main active metabolite of ART) could attenuate the proliferation of human mesangial cells induced by aggregated IgA1 through the mTOR signaling pathway in vitro [33]. Although there is a lot of current laboratory evidence that ART has a good regulatory effect on IgA nephropathy, there are still no high-quality randomized, placebo-controlled clinical trials to provide evidence of ART in the treatment of IgA nephropathy, which has limited the clinical use of ART in IgA nephropathy.

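### Safety versus placebo is a stated aim, but the only between-arm safety comparison is a chi-square/Fisher P-value with little power for uncommon events; risk differences with confidence intervals would serve better (minor)

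*Protocol article*

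**What the plan says.** Safety is one of the trial's questions. It is in the title, the Background calls the study "designed to estimate the efficacy and safety of ART in IgA nephropathy", and the Discussion gives the purpose as "to evaluate the efficacy and safety of oral ART versus placebo in patients with IgA nephropathy".

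The Statistical analysis section covers safety in one sentence. It begins "adverse events will be described according to the number of cases and percentage, and the chi-square test", and its comparison reads in full "the chi-square test and Fisher’s exact test will be used to analyze the differences between groups". The significance rule is general to all tests: "A 2-sided *P* < 0.05 will be defined as statistically significant". No risk difference, risk ratio, confidence interval or upper bound is named for adverse events. The sentence does not say whether the test is overall across three groups or pairwise. Overall is the more natural reading, because the efficacy tests named just before it (one-way ANOVA, Kruskal-Wallis) are overall tests.

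On size, the Sample size section says that "the sample size estimates were based on the change in proteinuria levels" and "we plan to enroll 120 participants (40 in each group) in the study". It states no adverse-event rate and no power for safety.

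**The concern.** The aim is worded as estimation, but the method named for comparing arms is a significance test. A test informs a safety question only as far as it can detect harm, and this trial's size was chosen for a continuous efficacy measure. For uncommon events, a non-significant result would be the likely outcome even if ART raised the risk materially. An overall three-group test also does not address the contrast named in the Discussion, ART against placebo, for either dose.

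This matters because the Background presents ART as a possible option with less toxicity than corticosteroids. A report of no significant difference in adverse events would then carry weight, while the data might still be compatible with a sizeable excess risk that nobody had displayed.

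**Working it through.** **Inputs from the article.** 40 per arm, 120 in total, allocated 1:1:1; 36 evaluable per arm before a 10% dropout allowance; two-sided alpha 0.05; chi-square and Fisher's exact tests. **Assumed, because the article gives none:** the adverse-event rates. A range is shown.

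**The plan's own figure.** There is no safety figure to reproduce. The efficacy figure is n = (0.8² + 0.5²)(1.960 + 1.282)² / 0.5² = 37.4 per arm, with power 0.889 at 36, close to the stated 36 and 90%. Using SD 0.8 for placebo and 0.5 for ART is my reading of the text. Then 36/0.9 = 40, and 3 × 40 = 120. The size therefore follows from proteinuria only.

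**Power of the three-group test for harm.** The statistic is X² = Σ(xᵢ − n·p̄)² / [n·p̄(1 − p̄)], with n = 40 and p̄ the pooled proportion. It is rejected above the 95% point of chi-square on 2 df. Power is the binomial probability of rejection summed over all 41³ outcomes. With the risk raised equally in both ART arms:

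| Placebo vs each ART arm | Detected | Missed |
|---|---|---|
| Doubling: 5% vs 10% | 10% | 90% |
| 10% vs 20% | 21% | 79% |
| 20% vs 40% | 50% | 50% |
| 30% vs 60% | 83% | 17% |
| Tripling: 5% vs 15% | 27% | 73% |
| 8% vs 24% | 48% | 52% |
| 10% vs 30% | 62% | 38% |
| 15% vs 45% | 88% | 12% |

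Power passes 50% at a placebo rate of 20.1% for a doubling and 8.3% for a tripling. If only one ART arm carries the harm, the points are 18.8% and 7.3%. If the lower dose carries half the excess, they are 23.8% and 9.9%. With 36 per arm and harm in both arms, they are 21.3% and 8.8%.

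**Other readings of the test.** Pooling ART (80) against placebo (40) by Fisher's test gives power 27% for 5% vs 15%, 23% for 10% vs 20% and 60% for 20% vs 40%. A pairwise comparison of 40 with 40 (normal approximation) gives 32%, 24% and 50%. The result for uncommon events does not depend on the overall reading.

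**What an interval adds.** Take 2/40 on placebo and 6/40 in each ART arm.
- p̄ = 14/120 and each expected count is 4.67. X² = (2.67² + 1.33² + 1.33²)/(4.67 × 0.883) = 2.59, P = 0.27.
- Pooled risk difference = 12/80 − 2/40 = 10 points. The Wilson limits are 8.8% to 24.4% for 12/80 and 1.4% to 16.5% for 2/40.
- Newcombe lower limit: 10 − √[(15 − 8.8)² + (16.5 − 5)²] ≈ −3 points. Upper limit: 10 + √[(24.4 − 15)² + (5 − 1.4)²] ≈ +20 points.
- For one dose alone (6/40 vs 2/40), the interval is about −4 to +25 points.

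**Zero events.** The upper limit of the two-sided exact 95% interval for the event rate is 1 − 0.025^(1/n): 4.5% for 0/80 and 8.8% for 0/40.

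**The case against.** Counts and percentages with chi-square or Fisher tests are conventional for adverse events, and low power for harm is normal in a trial sized for efficacy. The Discussion itself calls this a proof-of-concept study and makes longer studies a precondition for ART becoming an option. Adverse-event follow-up and a data safety monitoring board are also in place. Effect measures and interval methods are often left to an analysis plan, which is not shown. Anyone can compute intervals from the promised counts, and reporting them does not change the miss rates.

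Much of this stands, and it is why the point is minor. The sample size is not at fault. Adverse-event follow-up and the board protect patients but do not compare arms. What remains is that the article does name a method for the comparison, and that method suits an estimation aim poorly.

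Two stronger readings are tempting and not supported. A reader might infer that the test misses a doubling or tripling of risk as a general rule. That depends on the placebo rate, which the article does not give: a tripling from 10% or a doubling from 30% is usually detected, so for a broad outcome such as any adverse event the test may perform adequately. A reader might also infer that the plan will treat non-significance as evidence of safety. No passage says so, and no safety hypothesis or margin is set.

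**Conclusion.** The point holds in a limited form, as a cheap improvement rather than an error. The single between-arm safety comparison is a P-value. With 40 per arm it fails more often than not to detect a doubling of risk when the placebo rate is below about 20%, or a tripling when it is below about 8%. These thresholds assume equal harm in both ART arms and an overall chi-square test. They move by only a few percentage points under the alternative harm patterns and with 36 per arm. Whether the trial's safety events fall in that range is unknown from the article; specific or serious events may do so. Whatever the rates, a P-value without an interval does not show how large an excess risk the data leave open. Severity: minor.

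**What to change.** In the safety paragraph of the Statistical analysis section, make the comparison the risk difference versus placebo with a 95% confidence interval (Newcombe or exact), for each ART dose and for pooled ART. Apply it to the proportion of patients with any adverse event, any serious adverse event, ALT or AST above twice the upper limit, and acute kidney injury; the last two already appear in the article's Termination criteria. Where no event occurs, give the exact upper bound for the event rate. Keep the chi-square and Fisher P-values as descriptive only, and state that a non-significant P-value will not be taken as evidence of safety.

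The cost is a few sentences and a few table columns, with no new data or patients. The downside is that the intervals will be wide, so the safety statement will read less favourably.
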